### Neuroimaging

Structural brain changes such as white matter disease and atrophy are associated with increased delirium risk^74^ and cerebrovascular disease^75^ may be particularly important. MRI is the most commonly used imaging modality in neuroscience research, owing to lack of radiation exposure and high levels of tissue contrast and spatial resolution. However, MRI is expensive and challenging to perform in older confused patients in the acute hospital setting and only feasible in a subset of patients. In contrast, CT brain scanning is available as part of standard care for around 60% of older hospital patients either from the index admission or from previous encounters and around ~15% of these also have MRI.^76^

In ORCHARD-PS, we have taken a pragmatic decision to exploit brain imaging acquired as part of standard care, either CT or MRI, and to supplement this with research brain scans, currently CT-based, to obtain brain imaging for as many participants as possible and avoid bias by indication. A recently developed technology, PCCT, offers greater spatial resolution and the potential for better grey–white matter differentiation compared with conventional CT^77^ and is currently used for ORCHARD-PS research brain imaging for Oxford participants. The use of PCCT in our study will help better understand its added value over conventional CT in the older population at risk of delirium and dementia in whom MRI may not be feasible.

### Knowledge gaps and insights from related areas

Current delirium biomarker studies are limited by a focus on one, or at most a few, specific biomarkers of the systemic response, neuronal injury or brain imaging. Studies combining multimodal biomarkers informative for both the systemic response and the underlying brain status in delirium and future dementia are therefore required to provide insights into molecular pathways and systemic/brain interactions. The importance of brain imaging is illustrated by our recent observation that white matter disease modifies associations between infection and future dementia risk but not delirium-dementia risk associations, indicating that different mechanisms may link particular acute illness features to specific dementia subtypes. Multiomics and machine learning approaches to large-scale multimodal data^78^ may help identify feature groups at increased risk of delirium and dementia but have not yet been widely explored.^79 80^ Proteomics^81^ and genome-wide association studies (GWAS) implicate innate immune, metabolic, synaptic and vascular homeostasis pathways in dementia and also in proteomic ageing clocks.^82^,^84^ Overlap between omics findings in dementia and hallmarks of ageing^85^ and delirium might therefore be expected and is supported by preliminary GWAS and proteomics studies.^79 86^

### Strengths and limitations

Strengths of our study include the longitudinal design with prospective delirium ascertainment including in patients lacking capacity to consent to research and careful phenotyping enabling adequate adjustment for confounders, acquisition of multimodal biomarkers and multiple follow-up strategies to minimise selection and attrition bias. There are some limitations. First, daily delirium screening for all included patients is not possible owing to practical issues and resource constraints. However, regular real-time EPR review is undertaken by the study team including of daily ward round entries and nursing staff records for any acute changes in cognition minimising the chances of missing delirium. Second, although our study design mitigates loss to follow-up, it is nevertheless likely that some selective attrition of frail and multimorbid participants may occur. However, the use of indirect follow-up using medical records and death certificates will ensure some level of follow-up on all participants. Third, although blood samples are collected at baseline and at each follow-up visit, we do not perform serial blood collection during admission, and therefore we are unable to assess the temporal evolution of blood biomarkers between delirium onset and resolution. Fourth, our study is limited to the older population and our findings may not be generalisable to younger people or those from different settings.

In summary, ORCHARD-PS will provide a rich research resource for studies on the impact of acute illness on the ageing brain and specifically the mechanisms underlying delirium and future dementia risk. Findings will address important knowledge gaps and help identify potential therapeutic targets for delirium and dementia treatment and prevention.

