## Aims and objectives

The primary aim of the Oxford and Reading Cognitive Health After Recovery from acute illness and Delirium—Prospective Study (ORCHARD-PS) is to elucidate the pathophysiology of delirium and subsequent cognitive decline following acute illness in older people.

The main objectives are to:

Determine the multimodal (clinical, bloods, neuroimaging, digital) biomarker associations with delirium and new dementia to 3-year follow-up.Determine the predictors of poor outcome in patients with delirium, including length of stay, institutionalisation, readmission to hospital, cognitive decline and mortality.Assess the potential of advanced photon-counting CT brain imaging in providing enhanced information through better grey-white matter differentiation, spatial resolution and quantification of brain atrophy.

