### Participants and eligibility

Consecutive eligible patients are identified from the acute clinical care teams including the acute general medicine and SDEC teams. Participants are recruited as soon as possible after admission or SDEC assessment.

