### Delirium ascertainment

Delirium diagnosis is made by the principal investigator ([name]) in discussion with the research team at weekly lab meetings and after review of all study records, clinical records and information from informants in accordance with the DSM-V criteria. Participants who have some but not all of the DSM-V criteria are classified as subsyndromal delirium.

Delirium is defined by onset time as described previously^2^:

Prevalent: present on or within 48 hours of admission;Incident: developing at least 48 hours after admission;Any: presence of prevalent or incident delirium.Both: where patients with prevalent delirium have a further episode of incident delirium at least 48 hours after resolution of the previous delirium episode.

The duration of delirium is defined as the day of delirium diagnosis to the day of full resolution. Motor subtype is characterised as hypoactive, hyperactive or mixed. The aetiology of delirium is determined and may include one or more of infection, constipation, dehydration, medication, pain, new intracerebral event or other. The presence of pre-existing dementia diagnosis is used to classify delirium as delirium only versus delirium superimposed on dementia.

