### Blood biomarkers

We will extract baseline routine laboratory results (eg, white cell count, neutrophil/lymphocyte ratio, C reactive protein (CRP) level, microbiology) from ORCHARD-EPR.

Additional research blood samples (approximately 20 mLs) are collected for blood banking and storage at −80°C as follows:

Cytodelics-stabilised whole blood for flow cytometry.Whole blood (one 1.5 mL and three 500 µL samples).Buffy coat.EDTA plasma (three 500 µL samples).Lithium-heparin plasma (three 500 µL samples).Serum (three 500 µL samples).Tempus blood RNA tube.

Future biomarker analyses will include:

Flow cytometry for differential immune cell counts and feature characteristics.Cytokine panel (n ~40, eg, Luminex assay).CNS markers (plasma amyloid, τ, neurofilament light chain, glial fibrillary acidic protein, serum 100 beta protein, neurogranin).Proteomics (eg, Olink, ~5000 proteins).Transcriptomics.DNA extraction and Apolipoprotein E genotyping.

Blood sampling is performed at baseline and at each follow-up visit.

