### Statistical analyses

Demographic data will be summarised using descriptive statistics and comparison between delirium versus no delirium groups will be performed using the χ^2^ test for categorical data and t-test/analysis of variance for continuous data. The prevalence and incidence of delirium, including the subtype (hypoactive, hyperactive, mixed), and the severity and duration of delirium will be determined together with the prevalence of preadmission dementia diagnosis and incidence of new dementia diagnosis on follow-up including the subtype. Logistic regression will be used to determine the associates of delirium (any, and by subtype and severity) adjusted for covariates including demographic factors, infection, illness severity, baseline cognition, frailty and comorbidity and apolipoprotein E genotype.

Cox proportional hazards regression will be used to determine the HRs for new dementia on follow-up in participants with versus without delirium, adjusted for covariates as above and stratified by baseline brain imaging factors (small vessel disease, atrophy). Longitudinal cognitive data from all time points will be used to examine the evolution of cognitive impairment over time including in specific cognitive domains. Free text responses in the evaluation questionnaire will undergo thematic analyses to determine participants’ experience and understanding of the rationale for performing cognitive tests in hospital, and their perspectives on being informed about their brain health and the risk of developing dementia in future based on information collected in their hospital records.

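### The stated delirium regression pools blood drawn before and after delirium onset, so for time-varying markers that model alone cannot tell predisposition from consequence

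*Protocol article*

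**What the plan says.** The first main objective (Aims and objectives) is: "Determine the multimodal (clinical, bloods, neuroimaging, digital) biomarker associations with delirium and new dementia to 3-year follow-up".

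Research blood (Blood biomarkers): "Blood sampling is performed at baseline and at each follow-up visit". The baseline draw goes with recruitment, which has no fixed window (Participants and eligibility): "Participants are recruited as soon as possible after admission or SDEC assessment".

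Onset categories (Delirium ascertainment): "Prevalent: present on or within 48 hours of admission". Incident delirium starts 48 hours or more after admission, and the combined category is "Any: presence of prevalent or incident delirium". Table 1 records the prevalent or incident category and the date of onset.

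Model (Statistical analyses): "Logistic regression will be used to determine the associates of delirium (any, and by subtype and severity"), with adjustment for covariates. In the same paragraph, subtype means hypoactive, hyperactive or mixed. Prevalence and incidence are to be described, but onset time is not among the regression breakdowns.

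Limitation (Strengths and limitations): "we do not perform serial blood collection during admission". The article gives this as the reason why marker levels cannot be followed through an episode, from its onset until it resolves.

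**The concern.** Some participants with delirium will already be delirious when the baseline sample is drawn, and others will become delirious afterwards. A marker level in the first group may reflect the episode itself. In the second group it cannot, because the episode has not begun. The any-delirium coefficient averages the two, and splitting by motor subtype or severity does not separate them.

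This matters because the primary aim is pathophysiology. The CNS biomarkers section asks whether raised markers show pre-clinical dementia or damage set off by delirium. The section on the systemic response describes inflammation as a trigger of delirium. Both ideas depend on whether the sample came before or after onset. A pooled association could be read either way.

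The disclosed limitation is a different one. It concerns the course of a marker within an episode, from onset to resolution. It does not tell the reader that the main contrast combines pre-onset and post-onset blood.

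The point applies to markers that change with illness, such as cytokines, CNS proteins, proteomics, transcriptomics and immune cell counts. APOE genotype is fixed and unaffected.

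**Working it through.** **1. The plan's own figures (Sample size).** They reproduce, and none is in dispute.
- Delirium cases for 10 predictors: 10 × 10 = 100.
- Dementia cases for 5 predictors: 5 × 10 = 50.
- Delirium without dementia: 50 / 0.60 = 83.3, taken as 83. Doubled: 166.
- Cohort: 166 / 0.30 = 553.3, taken as 553. Participants without delirium: 553 − 166 = 387.

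**2. Does the stated model resolve timing?**
- There is one in-hospital draw, at recruitment, not timed to onset.
- The outcome is any delirium, prevalent and incident together.
- The breakdowns are motor subtype and severity. Neither depends on whether onset came before or after the draw.
- Onset category and date are recorded, so the gap is in the model and not in the delirium data.

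**3. Size of the mixing (illustration).** The documents give no prevalent/incident split and no effect size. Let p be the share of cases sampled before onset, using the incident share as a rough proxy. Let d_post and d_pre be the marker differences from participants without delirium. Then

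pooled difference = (1 − p) × d_post + p × d_pre.

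| Assumed p | d_post = 0.5, d_pre = 0 | d_post = 0, d_pre = 0.5 |
|---|---|---|
| 10% | 0.45 SD | 0.05 SD |
| 20% | 0.40 SD | 0.10 SD |
| 30% | 0.35 SD | 0.15 SD |

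A pure consequence of delirium passes almost undiminished into the pooled estimate. A pure pre-onset signal nearly vanishes.

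**4. What a pre-onset analysis could support.** Predictors are cases / 10. Power is for a 0.3 SD difference (assumed) against 387 participants, two-sided 0.05, unadjusted: Φ(0.3 × √(n₁n₂/(n₁+n₂)) − 1.96).

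| Cases | n | Predictors | Power |
|---|---|---|---|
| Any delirium | 166 | 16 | 90% |
| Pre-onset, p = 10% | 16.6 (about 17) | about 1 | 22% |
| Pre-onset, p = 20% | 33.2 (about 33) | about 3 | 38% |
| Pre-onset, p = 30% | 49.8 (about 50) | about 5 | 51% |

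The plan assumes 10 predictors for delirium. One caution: the Sample size section describes the 166 as having delirium at baseline, yet derives the cohort from an overall occurrence of 30%. Using 166 as the denominator for incident cases is therefore approximate.

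**The case against.** **The article is condensed.** Splits of a banked-sample analysis may sit in a fuller document, and nothing excludes onset-specific models. This has some force. But the article does list the breakdowns and leaves out the one that bears on its own question, and its limitation describes the consequence of single sampling too narrowly. If a split is already planned, one sentence would say so.

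**The objective is association only.** The text speaks of associations and associates, so reading the coefficient as a risk marker is an inference. That is fair for the model taken alone. The pathophysiological aim and the CNS biomarkers discussion nevertheless invite the directional reading.

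**A reader might infer that the study cannot separate predisposition from consequence at all.** The documents do not support that. The restriction applies to the pooled coefficient, because onset dates allow a split. Samples at 3 months, 1 year and 3 years also bear on whether changes persist.

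**A reader might equate prevalent with sampled after onset and incident with sampled before it.** That is only a proxy. Prevalent delirium includes onset up to 48 hours after admission, so an early draw may precede it. A late baseline draw may follow incident onset. Timing of the sample relative to onset is the sounder division.

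**Splitting costs precision, and any delirium underlies the sample size.** This stands, and it is why any delirium should not be demoted. Low precision in one part does not, however, make the pooled coefficient interpretable as to direction.

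**If nearly all cases are sampled after onset, splitting changes little.** At p = 10% the pooled 0.45 SD is close to 0.5 SD. True, but the reader then needs to know that the estimate is almost wholly post-onset.

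**Conclusion.** The point holds as a defect of the stated model and its stated limitation, not of the data collection. For time-varying blood markers, the any-delirium regression mixes pre-onset and post-onset samples, and on its own it cannot address the question that the article raises about pre-existing disease versus consequence. The any-delirium estimate remains a valid overall association.

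The size is illustrative. A 0.5 SD difference confined to post-onset samples would appear as 0.35-0.45 SD, and one confined to pre-onset samples as 0.05-0.15 SD, if 10-30% of cases are sampled before onset. Both the effect and the share are assumptions. Even a clean pre-onset analysis would establish temporal order, not causation. The change is worth making before the biomarker analyses begin.

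**What to change.** **Statistical analyses.** Keep any delirium as the overall analysis. Add that associations for time-varying blood markers will also be reported by sample timing relative to recorded onset:
- (a) delirium developing after the draw, among participants free of delirium at the draw;
- (b) delirium already present at the draw, adjusted for days from admission to sampling. Days from onset will not serve as a covariate here, because participants without delirium have no onset.

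**Sampling date.** Table 1 lists blood banking by visit but states no date. Confirm that the date of each baseline draw is kept. The split depends on it.

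**Strengths and limitations.** Add a sentence saying that the any-delirium analysis combines samples drawn before and after onset and does not by itself separate predisposition from consequence.

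**Cost.** Analysis wording only, with no new data collection, provided that sampling dates are held. The price is precision in (a): about 17-50 cases at an assumed 10-30% share, hence about 1-5 covariates under the rule of 10. That analysis should be declared imprecise in advance and reported with intervals, and a null result should not be read as absence of a pre-onset signal.

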## Ethics and dissemination

ORCHARD-PS is approved by the South Central- Berkshire Research Ethics Committee (REC Reference: 23/SC/0199). Results will be disseminated through peer-reviewed publications and conference presentations and lay interest groups. Anonymised data will be made available to external researchers at project end, which will be defined as the completion of publications by the study team.
